#### Intervention

All enrolled patients will receive four containers with the following ointments: 1% simvastatin-acid sodium salt, 1% atorvastatin calcium salt, and two vehicle ointment-filled containers labeled with a preselected limb as follows: “left upper limb”, “right upper limb”, “left lower limb”, and “right lower limb”. In each case, application of an active substance to a particular limb is associated with application of the vehicle ointment onto the opposite limb as previously described. The exact description of the randomization process is presented below.

Study participants will apply ointments twice daily (every 12 h) according to the container labels. An approximate amount of 1 cm of ointment is advised for palm-sized lesions. Study drugs must be stored at room temperature.

During the study period, participants are not allowed to initiate treatment with systemic statins due to any other medical conditions. In case of a necessity to start statin uptake during the study period, the patient’s participation will be prematurely terminated. Moreover, administration of any other topical active substances on lesional areas is forbidden throughout the study period. The systemic use of any immunosuppressive or immunomodulating medications, as well as laser therapy or phototherapy, is not allowed throughout the study.

Participants are not allowed to use any other additional vitiligo treatment, either systemic or topical, including the use of antioxidants, *Ginkgo biloba*, or dermocosmetics.

The study period was defined as 12 weeks. The visit schedule includes a screening visit, when all necessary data including blood sample results will be gathered, baseline (week 0) and three evaluation visits every 4 weeks (week 4, week 8, and week 12). During each visit all participants will be provided with a new set of previously weighed study drugs. Previously distributed containers need to be returned at each visit, and their final weight will be recorded in the study documentation after return. Photographic documentation of vitiligous lesions will be recorded during each visit.

Sunbathing is prohibited throughout the whole study period.

#### Randomization and blinding

Randomization of study participants into the arms was performed using Random Allocation Software version 1.0. The study was designed as a double-blind trial. The preparation of study drugs, as well as the process of blinding, was performed by the Department of Pharmaceutical Technology, Nicolaus Copernicus University, Faculty of Pharmacy in Bydgoszcz. The study drugs are delivered in identical containers labeled with the consecutive participant number and an assigned application area, i.e., “left upper limb”, “right upper limb”, “left lower limb”, or “right lower limb”. The weight of all containers is identical at the moment of delivery. Organoleptic properties, including color, consistency, tenacity, and smell of the studied ointments are highly similar, thus making the substances indistinguishable for both participant and investigator.

#### Primary outcome

The primary outcome of the study was defined as the evaluation of repigmentation of vitiligous lesions achieved after the administration of 1% simvastatin-acid sodium salt or 1% atorvastatin calcium salt ointments compared with vehicle ointments after a 12-week study period. Repigmentation will be assessed according to VASI and BSA scales based on photographs obtained during each visit using planimetry software as mentioned above.

#### Secondary outcomes

Secondary outcomes of the study comprise safety and tolerability of the study drugs, assessed as the number of participants with treatment-related adverse events according to Common Terminology Criteria for Adverse Events (CTCAE) version 4.0, the percentage of patients who achieved particular response rates (none, 0%; poor, 1–25%; moderate, 26–50%; good, 51–75%; excellent, > 75%) in each arm assessed as a relative reduction in lesional skin area, as well as with the BSA and VASI scale, a comparison of simvastatin and atorvastatin efficacy between study participants, the association between disease duration and repigmentation rate in the study arms, and the association between estimated daily ointment use (grams per square centimeter of skin) and the repigmentation rate in study arms.

The complete list of study outcomes is presented in Table 2.

**Table 2 Tab2:** A complete list of the EVRAAS study outcomes

Primary outcome	Secondary outcomes
1. Evaluation of repigmentation of vitiligous lesions achieved after the administration of 1% simvastatin-acid sodium salt or 1% atorvastatin calcium salt ointments compared with vehicle ointment after a 12-week study period (change from baseline in repigmentation on BSA and VASI scale).	1. Number of participants with treatment-related adverse events as assessed by CTCAE version 4.0 2. Percentage of patients who achieved particular response rate in each arm assessed as a relative reduction in lesional skin area as follows: none, 0%; poor, 1–25%; moderate, 26–50%; good, 51–75%; excellent, > 75% 3. Percentage of patients who achieved particular response rate in each arm assessed as a relative reduction in BSA scale as follows: none, 0%; poor, 1–25%; moderate, 26–50%; good, 51–75%; excellent, > 75% 4. Percentage of patients who achieved particular response rate in each arm assessed as a relative reduction in VASI scale as follows: none, 0%; poor, 1–25%; moderate, 26–50%; good, 51–75%; excellent, > 75% 5. Comparison of simvastatin and atorvastatin efficacy between study participants 6. The association between disease duration and repigmentation rate in study arms 7. The association between estimated daily ointment use (grams per square centimeter of skin) and repigmentation rate in study arms

*BSA* body surface area, *CTCAE* Common Terminology Criteria for Adverse Events, *VASI* Vitiligo Area Scoring Index

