**Discussion:**

Currently available vitiligo topical therapeutic approaches including calcineurin inhibitors and corticosteroids remain poorly effective and are associated with either relatively high cost or potentially dangerous adverse effects. The clinical application of orally administrated statins, widely used as systemic cholesterol-lowering agents, in vitiligous patients has only been tested in two clinical trials; however, data on their potential usefulness is scarce. Moreover, due to a high risk of clinically significant toxicity, topical administration was recommended by researchers. This study is the first to evaluate safety and efficacy of the topical use of statins in patients presenting with NSV.

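### The safety outcome is one participant count under shared exposure, so any local reactions that occur cannot be attributed to either statin or compared with vehicle

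*Protocol article*

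**What the plan says.** The Secondary outcomes section of the protocol article sets out to assess "safety and tolerability of the study drugs, assessed as the number of participants with treatment-related adverse events". Table 2, presented there as the full list of outcomes, repeats the definition as item 1: "Number of participants with treatment-related adverse events as assessed by CTCAE version 4.0". Neither place splits the count by ointment, limb or arm. Items 2 to 4 of the same table do carry a split, for example "Percentage of patients who achieved particular response rate in each arm assessed as a relative reduction in lesional skin area".

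The Intervention section gives everyone the same exposure: "All enrolled patients will receive four containers with the following ointments: 1% simvastatin-acid sodium salt, 1% atorvastatin calcium salt, and two vehicle ointment-filled containers". Use is concurrent: "Study participants will apply ointments twice daily (every 12 h) according to the container labels". Allocation is to limbs within a person: "application of an active substance to a particular limb is associated with application of the vehicle ointment onto the opposite limb".

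Safety is a declared aim. The Discussion part of the abstract states: "This study is the first to evaluate safety and efficacy of the topical use of statins in patients presenting with NSV".

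**The concern.** Treatment is allocated to limbs, but safety is counted in whole participants with no split by treatment. Nobody receives only one statin, and nobody receives only vehicle, so participants cannot be divided into groups that differ in exposure. The outcome as worded gives one proportion without a comparator.

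Limiting the count to treatment-related events does not supply that comparator. The Randomization and blinding section says that neither participant nor investigator can tell the ointments apart. The Design section says that active and vehicle ointments share an absorption base with a sorption promotor. A local reaction can therefore be judged related to treatment and still come from the base. Only the contrast with the opposite vehicle limb separates drug from base.

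At stake is whether the trial can say that either statin ointment irritates the skin more than its base. The Discussion of the article rests part of its case for topical statins on a favourable safety and tolerability profile, and it expects the results to inform larger trials.

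**Working it through.** The plan states no figure for this outcome, so there is nothing to reproduce. The check asks what the stated count can identify.

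**Inputs from the article**
- Sample size: at least 24 participants (Sample size calculation). I use n = 24.
- Limbs per participant: one simvastatin, one atorvastatin, two vehicle (Intervention).
- Limbs in total: 24 simvastatin, 24 atorvastatin and 2 × 24 = 48 vehicle. Each active limb is paired with a vehicle limb in the same person.

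**Assumptions, for illustration only**
- Per-limb probabilities of a local event are s (simvastatin), a (atorvastatin) and v (vehicle), independent across limbs. The article gives no event rates.

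**Step 1. What the participant count estimates**

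P(participant has at least one event) = 1 − (1 − s)(1 − a)(1 − v)²

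This is one equation in three unknowns. Take a participant-level risk of 25%, that is 6 of 24 (exact 95% CI 9.8% to 46.7%). Each row below gives exactly that risk:

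| Source of risk | s | a | v | Calculation |
|---|---|---|---|---|
| Simvastatin only | 25% | 0 | 0 | 1 − 0.75 = 0.25 |
| Atorvastatin only | 0 | 25% | 0 | 1 − 0.75 = 0.25 |
| Vehicle only | 0 | 0 | 13.4% | v = 1 − 0.75^(1/2) = 0.134 |
| All limbs equal | 6.9% | 6.9% | 6.9% | 1 − 0.75^(1/4) = 0.069 |

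The same count fits four quite different safety profiles. The values are arbitrary, but the inability to separate them is not: any positive count has the same property.

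**Step 2. What the count can still show**

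A participant with an event on the simvastatin limb is a participant with an event. So s cannot exceed the participant-level risk, and the same holds for a. This needs no independence assumption. With 0 of 24:
- one-sided 95% upper limit = 1 − 0.05^(1/24) = 0.117
- two-sided 95% upper limit = 1 − 0.025^(1/24) = 0.142

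Zero events would thus bound each drug's risk at 11.7% (one-sided) or 14.2% (two-sided).

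**Step 3. What limb recording adds, and its limit**

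With the limb recorded, each statin has 24 within-person pairs against vehicle, and the four rows above become distinguishable. A formal test has little reach at this size. With k discordant pairs all in one direction, the two-sided exact McNemar p-value is 2 × 0.5^k. For k = 5 it is 0.0625; for k = 6 it is 0.031. At least 6 of 24 participants (25%) would have to react on the statin limb only, with none reacting on the vehicle limb only. The comparison should therefore be descriptive.

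The 48 vehicle limbs belong to 24 people and should not be treated as 48 independent observations.

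**The case against.** The strongest reply is that the article does not say that events will be recorded without a site or reported only as a pooled total. Items 2 to 4 also count patients while splitting by arm, so a count of participants is compatible with tabulation by ointment. Containers carry limb labels, so limb can be linked to ointment after unblinding. The adverse event form, full protocol and analysis plan are not shown and may record the limb.

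Much of this stands. A reader might infer that the within-patient control is thrown away; nothing in the article says so, and the design keeps it available. The point that remains is narrower. The outcome is stated, its list is presented as complete, and the split given to the response outcomes is absent from safety. That is a stated definition that does not fit the allocation, not merely a detail left to another document.

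A reader might also infer that the trial can show nothing about either drug's safety. That goes too far, because zero events would still set an upper limit for each. Nor is the inability to assign systemic events to one statin a fault of this outcome. It follows from applying both drugs at once, and no rewording removes it.

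Finally, this is a pilot, and a paired test at n = 24 detects only large differences. That is correct, and it argues for description rather than testing. It does not argue for a count without a comparator.

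**Conclusion.** The point holds for local reactions. As worded, the safety outcome is one uncontrolled proportion in at least 24 participants who share the same exposure. Once any event occurs, it cannot attribute a local reaction to simvastatin, atorvastatin or vehicle, and it does not use the opposite vehicle limb. This conclusion rests on the stated outcome and exposure alone; the event rates above only illustrate it. With no events the count remains informative, with a one-sided 95% upper limit of 11.7% for each drug at n = 24.

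This should be corrected. It concerns a secondary outcome and leaves the efficacy analysis untouched, but safety is a declared aim and the better definition costs almost nothing.

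**What to change.** - Redefine the outcome as the number of participants with application-site adverse events (CTCAE version 4.0) on the simvastatin limb, on the atorvastatin limb, and on the vehicle limb opposite each.
- Record the affected limb for every local event, whatever its judged relation to treatment. Keep the relatedness judgement as an additional item.
- After unblinding, report for each statin the paired active-minus-vehicle difference in proportions with an exact confidence interval. State that this is descriptive at n = 24.
- Report systemic events per participant for the combined exposure only, and state that they cannot be assigned to one drug.

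The cost is one limb field on the adverse event form and a reworded outcome. Treatment, visits, randomisation and sample size do not change. The Trial status section says recruitment is under way, so the field should be added early, because the limb may be hard to recover reliably later. If the form already records it, only the wording needs to change.

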## Discussion

The treatment of vitiligo remains poorly effective and is still a great challenge for dermatologists. Thus, numerous clinical studies aiming to develop a drug that inhibits vitiligo progression and induces skin repigmentation are currently ongoing. Acral depigmentation is considered to be particularly difficult to treat. Methods for topical treatment of vitiligo are still limited. Topical substances commonly used to treat vitiligo include corticosteroids and calcineurin inhibitors [19]. Chronic use of topical calcineurin inhibitors is associated with a relatively high cost, which is unaffordable for a noticeable number of patients. Moreover, the efficacy of calcineurin inhibitors is limited. The best effects of treatment with calcineurin inhibitors were reported in patients applying them on facial and neck lesions [20]. Topical corticosteroids, although significantly cheaper, may induce various adverse events if applied chronically. This in turn may result in an increase of therapeutic costs due to the required treatment of adverse effects. Preparation of statins ointments is a low-cost process. Taking into account estimated the positive safety/tolerability profile of topical statins, these agents may turn out to be a potential alternative for current vitiligo topical treatment.

Patients treated with other nonsurgical methods such as phototherapy (narrow band UVB 311 nm, UVA, PUVA-therapy), 308 nm laser therapy, administration of antioxidants, *Ginkgo biloba*, or systemic immunosuppressive agents (e.g., methotrexate, corticosteroids) or combination therapies often do not achieve desirable improvement.

The use of statins is associated with an increase in anti-inflammatory cytokine secretion and inhibition of proinflammatory cytokine production, as well as with a shift from a Th1- to Th2-dependent immunological response as described above. Taking into consideration the postulated immunological pathogenesis of vitiligo it becomes a rationale for potential implementation of statins for its treatment.

Until now, topical administration of statins in various medical conditions including wounds, dry-eye, pressure ulcers, and chronic periodontitis has not been associated with serious adverse events [21–24].

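### The only listed safety outcome counts just the adverse events judged treatment-related, a judgement that this design cannot check for systemic events and does not need for local ones

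*Protocol article*

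**What the plan says.** The protocol article fixes the safety outcome in two places that agree. The running text under Secondary outcomes lists "safety and tolerability of the study drugs, assessed as the number of participants with treatment-related adverse events", and Table 2, secondary outcome 1, reads "Number of participants with treatment-related adverse events as assessed by CTCAE version 4.0". The same section adds: "The complete list of study outcomes is presented in Table 2".

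On exposure, the Intervention section says: "All enrolled patients will receive four containers with the following ointments: 1% simvastatin-acid sodium salt, 1% atorvastatin calcium salt, and two vehicle ointment-filled containers". It also says that "application of an active substance to a particular limb is associated with application of the vehicle ointment onto the opposite limb". The control is thus a limb of the same person. No participant receives vehicle only.

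Safety is presented as a purpose of the trial. The Discussion paragraph of the Abstract says: "This study is the first to evaluate safety and efficacy of the topical use of statins in patients presenting with NSV". It gives the reason for the topical route as follows: "due to a high risk of clinically significant toxicity, topical administration was recommended by researchers".

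**The concern.** A relatedness filter decides which events enter the safety result before any comparison is made. Its value depends on how well relatedness can be judged, and here that differs by type of event.

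- **Systemic events** belong to the person, and every person is exposed to both statins. Blinding hides which limb carries which ointment, but it cannot create an unexposed person. A judgement that an event is unrelated cannot be checked against any comparison within the trial.
- **Local events** belong to a limb, and each statin limb has a blinded vehicle limb opposite. The difference between limbs estimates the drug effect without anyone's opinion on cause. A single count per participant, filtered by opinion, does not use that comparison.

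At stake is how a low count would be read. It could mean that few events occurred, or that events occurred and were attributed elsewhere. Outcome 1 as defined cannot separate the two, yet it is the only listed outcome that speaks to safety in what is described as the first such evaluation.

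**Working it through.** The article states no event rate, power or target for safety, so there is no figure of the plan's own to reproduce. The check is a reading of the definition, followed by an illustration.

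**1. Is outcome 1 the only safety outcome?** Table 2 has one primary and seven secondary outcomes. The primary is repigmentation. Secondary outcomes 2 to 4 are response categories by lesional area, BSA and VASI. Outcome 5 compares the two statins for efficacy. Outcomes 6 and 7 relate repigmentation to disease duration and to ointment use. That leaves outcome 1 alone, in a list that the article calls complete.

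**2. What comparison does the design offer?**

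| Type of event | Unit affected | Statin-free comparator | Does relatedness have to be judged? |
|---|---|---|---|
| Systemic | participant | none, since all receive both statins | it can only be judged, not checked |
| Application site | limb | opposite limb, vehicle, blinded | no, the limb contrast suffices |

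**3. What does the filter do to the count?** Let n = 24 (the minimum in Sample size calculation), p = the share of participants with a systemic event, and s = the share of those judged related. Both p and s are assumptions; the article gives neither.

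Expected count = n × p × s. Chance of at least one counted = 1 − (1 − p·s)^24.

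| p | s = 1 (all counted) | s = 0.5 | s = 0.25 |
|---|---|---|---|
| 5% | 1.2; 71% | 0.6; 46% | 0.3; 26% |
| 10% | 2.4; 92% | 1.2; 71% | 0.6; 46% |
| 20% | 4.8; 99.5% | 2.4; 92% | 1.2; 71% |

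For p = 20%, the chance of reporting no event is 0.80^24 = 0.5% with all events counted, 0.90^24 = 8% with s = 0.5, and 0.95^24 = 29% with s = 0.25.

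**4. What would a zero mean?** With 0 of 24, the one-sided 95% upper limit is 1 − 0.05^(1/24) = 11.7%. If all events are counted, this limit applies to p. Under the filter it applies to p × s. If s were known to be 0.5, the limit for p would be 11.7 / 0.5 = 23.4%; at s = 0.25 it would be 11.7 / 0.25 = 46.8%. Since s is not known, a zero under outcome 1 sets no usable limit on p.

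**The case against.** The strongest objection is that counting all events does not supply the missing comparator. In 24 or more people who are all exposed, an all-cause count over 12 weeks mixes drug effects with background illness and cannot establish systemic safety either. This stands. The change makes the result complete and transparent, but it does not make it controlled.

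Second, events outside outcome 1 need not go unreported. The article commits to Good Clinical Practice and to analysis of all data obtained, and the full protocol may tabulate every event. This also stands. A reader might infer that unrelated events will vanish from the trial's reports, but the text shows only that they lie outside the declared outcome.

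Third, a reader might infer that attribution will lean towards calling events unrelated, because the Discussion already speaks of "Taking into account estimated the positive safety/tolerability profile of topical statins". The documents do not support that. The phrase belongs to an argument about alternatives to current topical treatment and is not an attribution rule. The article does not say who assesses relatedness or by what criteria, and timing or course may inform the judgement. The toxicity cited in the Abstract, together with the knowledge that everyone receives statins, could push attribution the other way.

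Fourth, for local reactions a judgement made blind to limb should not favour either side while blinding holds. That is fair. The argument there is that the filter is unnecessary and discards events, not that it biases the limb contrast.

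What the objections do not remove is the definition itself. It is stated twice, sits in a list called complete, and is not a detail left to another document.

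**Conclusion.** The point holds as a weakness in a stated definition. The trial's only listed safety outcome excludes any event judged unrelated. For systemic events that judgement has no unexposed participant to check it, and for local events it is not needed.

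The size cannot be derived from the article. For any given p, the expected count falls in proportion to the share judged related; the probabilities above only illustrate assumed values of p and s. They also say nothing about whether an exclusion is mistaken, since some events judged unrelated will truly be so. The direction and size of any attribution bias are unknown, and so is the extent of any systemic effect of topical use.

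No efficacy result and no sample size depends on this. It is an inexpensive improvement to one secondary outcome of a pilot trial, worth making because safety is a stated aim.

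**What to change.** 1. Redefine secondary outcome 1 as the number of participants with any adverse event starting after the first application, by CTCAE version 4.0 grade, regardless of attributed cause. Show the treatment-related subset in an adjoining column.
2. Report application-site events by limb, each statin against its vehicle limb, regardless of attributed cause.
3. State that systemic events have no statin-free comparator in this design, so their counts are descriptive and cannot establish systemic safety.

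The cost is the wording of one outcome and an extra table column, plus the breakdown by limb. An adverse event has to be recorded before its relatedness can be judged, so the overall count should need no new data; the limb breakdown needs the affected limb to be noted. The downside is a higher headline count that includes incidental events, which the adjoining column puts in context.
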